### Statistical Analysis

Responses to questionnaires and test scores will be imported from the LimeSurvey platform and compiled into a Microsoft Excel file. Descriptive statistics (means, SDs, frequencies, and percentages) will be used to summarize sociodemographic data.

An analysis of covariance will be performed to detect postintervention differences between groups for the primary and secondary measures using the respective T1 score as the covariate. Dropout rates and reasons will be reported. Depending on the nature of the missing data (proportion of missing values), appropriate methods will be chosen with careful consideration of the data structure and the underlying assumptions. The significance level will be set at .05, and all statistical tests will be 2-tailed. The scores from the self-reported questionnaires on walking aid knowledge and confidence will be summed and analyzed using an appropriate parametric test (if normally distributed). Retention of balance confidence, mobility, and self-reported score of knowledge in the experimental group will be evaluated using 2-tailed paired *t* tests. Sensitivity analyses will also be conducted based on walking aid type, walking aid use experience, previous training, and the main reason for use. All analyses will be performed in SPSS software (version 27; IBM Corp).

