**Methods:**

A 2-site single-blind pragmatic randomized controlled trial is proposed. A total of 52 adults who use walking aids will be recruited through clinical and community organizations. Participants will complete measures of balance confidence (Activities-specific Balance Confidence scale; the primary outcome), mobility (6-Minute Walk Test and Timed Up and Go test), walking aid skills (Walking Aids Skills Test, WAST), and knowledge of and confidence in walking aid fit and use (self-reported questionnaire) at baseline (T1). Participants will then be randomly assigned to the experimental (ICanWALK app) or attention-matched control group (breathing activity app) and will complete two 20-minute sessions interacting with the assigned app. Participants will be reassessed 2 to 4 days after the intervention (T2) and again 4 weeks later (T3). Analysis of covariance will be performed for primary and secondary outcomes by using SPSS software.

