#### Control Group

The control group will be attention matched to mimic the time, location, and contact with a trainer of the experimental group [50]. Participants will follow the same schedule as the experimental group but will also complete a breathing exercise module available on the MOVE Improve app. The modules are identical in layout, instruction, and self-assessment of videos to the ICanWALK app but differ in content, as no information related to walking aids and mobility is included in this program (Figure 3). With assistance from a trained health professional student or a research assistant, participants in the control group will complete 2 separate 15- to 20-minute sessions within 1 week. Participants will select the breathing exercise module and then choose the specific skill they wish to practice (eg, breathing exercise for reduced stress and breathing exercise for increased lung function), watch the instructional video, and review the performance criteria. A video of the participant performing the selected skill is then recorded and uploaded alongside the model video to allow for side-by-side comparison. The participant will review the video in the app and compare it to the demonstration video to determine whether each component of the skill was performed correctly. A score will be generated at the end.

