### Study Procedure and Data Collection

The study procedures (timeline and measurement tools) are illustrated in the SPIRIT checklist (Table 1). Participants will be assessed at 3 time points: baseline (T1), after intervention (T2), and 4-week follow-up (T3). After signing the consent form, a study coordinator will schedule the first evaluation session (T1). Preintervention questionnaires will include sociodemographic data (eg, age, sex, gender, walking aid type, reasons for using the walking aid, the duration of walking aid use, and previous walking aid experience), the ABC questionnaire, and self-reported knowledge and confidence in fitting and using the walking aid using a tablet or laptop. Participants will then complete the Walking Aids Skills Test (WAST) and mobility tests (6-Minute Walk Test, 6MWT and Timed Up and Go, TUG test).

**Table 1 table1:** SPIRIT (Standard Protocol Items Recommendations for Intervention Trials) checklist.

Schedule of activities		Enrollment	Assessment	Allocation	After allocation				Closeout
		Screening	Baseline (T1)		Intervention	After intervention (T2)	4-wk follow-up (T3)		

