**Assessments**									
	Activities-specific Balance Confidence scale		✓			✓	✓		
	Self-reported walking aid knowledge and confidence		✓			✓	✓		
	Timed Up and Go test		✓			✓	✓		
	6-Minute Walk Test		✓			✓	✓		
	Walking Aid Skills Test		✓			✓	✓		

^a^ICanWALK: Improving Canadians’ Walking Aid Skills, Learning, and Knowledge.

All data will be collected by an assessor who will be blinded to group allocation. The T1, postintervention (T2), and follow-up (T3) questionnaires will be imported into the LimeSurvey platform to allow for completion during the evaluation while ensuring secure data management. The collected data will be anonymized with a code assigned to each participant and will be stored on the institutional platform. Access to data will be limited to authorized personnel.

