### Limitations

This study may have several limitations. First, we will include participants who use various types of walking aid, but we will not stratify them according to type of walking aid, their digital literacy, cognitive level, user experience, or education. This may result in inconsistent responses to the app. However, sensitivity analyses will help to partially address this issue. Furthermore, participants with cognitive impairments or vision or hearing limitations may face barriers to fully engaging with the app. Second, the primary outcome is a self-reported measure, and this may be subject to measurement bias, such as social desirability bias or recall bias. We believe that the study design, methodology, and expected sample size make the expected results plausible. Finally, this study focuses on a short-term follow-up period and may not capture the long-term efficacy of the app. The key strength of this study will be the use of video-based feedback, as it enables the motor learning process and skills acquisition, leading to high memorization, behavioral change, and performance [69,71,76,77].

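### Retention is tested only by paired t tests within the experimental arm, and no between-arm contrast at T3 is specified although both arms are measured then

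*Protocol article*

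**What the plan says.** **Retention.** Statistical Analysis: "Retention of balance confidence, mobility, and self-reported score of knowledge in the experimental group will be evaluated using 2-tailed paired" *t* tests. The sentence names no pair of visits, retention margin or decision rule. It covers balance confidence, mobility and self-reported knowledge; the WAST is not listed.

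**Between-group analysis.** Same section: "An analysis of covariance will be performed to detect postintervention differences between groups for the primary and secondary measures using the respective T1 score" as covariate. The general rule is "The significance level will be set at .05, and all statistical tests will be 2-tailed".

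**Visit labels.** Study Procedure and Data Collection, below Table 1: "The T1, postintervention (T2), and follow-up (T3) questionnaires will be imported into the LimeSurvey platform". Postintervention is the label for T2, and T3 carries a separate label, follow-up.

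**Data available.** Study Procedure and Data Collection: "Participants will be assessed at 3 time points: baseline (T1), after intervention (T2), and 4-week follow-up (T3"). The Control Group section adds: "Participants will follow the same schedule as the experimental group". Table 1 marks all five measures, including the WAST, at T1, T2 and T3. The abstract gives the timing: "Participants will be reassessed 2 to 4 days after the intervention (T2) and again 4 weeks later (T3").

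**The concern.** The trial randomises against an attention-matched control so that time, contact with a trainer and repeated testing cancel out of the comparison. For the 4-week question the stated method does not use that control. A test inside one arm shows whether scores in that arm moved. It does not show whether they differ from what the same people would have scored without the app.

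The unnamed visit pair leaves two readings, and neither estimates an app effect at T3:

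- **T1 against T3.** The change includes whatever both arms gain from a third ABC, 6MWT and TUG, from attention and from time.
- **T2 against T3.** The test looks for a loss. Without a margin, a non-significant result is compatible with retention, with partial loss and sometimes with full loss.

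At stake is the interpretation of the only follow-up visit. The T2 comparison of the primary outcome is not affected.

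**Working it through.** **Inputs**

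- The protocol gives no figure for the retention analysis.
- Gain of 9.2 points, Cohen *d* 0.59 and correlation 0.5: Sample Size section.
- SD = 9.2/0.59 = 15.6. The protocol does not state this SD. It is back-calculated, and the article does not say which SD standardised *d*, so it is an assumption.
- Correlations: 0.5 (Sample Size), 0.85 (the test-retest ICC in the Primary Outcome section) and 0.7 as a value between them. Applying any of these to the T2–T3 or T1–T3 pair is an assumption.
- Numbers: 45 evaluable gives 22 or 23 per arm; 52 randomised gives 26 per arm.

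The planned 45 does not follow from *d* = 0.59 (f = 0.295) at 90% power and correlation 0.5. The group-by-time interaction gives 33, and the between-group test or an ANCOVA gives 93. An interaction with f = 0.25 gives 45, but that value is not stated. The present point does not depend on this, since 45 is used only as the evaluable number.

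**Step 1: T2 against T3, experimental arm, n = 22**

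SD of change = 15.6 × √(2(1 − r)). Noncentrality = loss × √n / SD of change. Two-sided critical value t(0.975; 21) = 2.08. CI half-width = 2.08 × SD of change / √22.

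| r | SD of change | p>.05 if 4.6 points are lost | p>.05 if 9.2 points are lost | 95% CI half-width |
|---|---|---|---|---|
| 0.5 | 15.6 | 74% (noncentrality 1.38) | 25% (2.77) | 6.9 |
| 0.7 | 12.1 | 60% (1.79) | 7% (3.57) | 5.4 |
| 0.85 | 8.5 | 33% (2.53) | 0.2% (5.05) | 3.8 |

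With n = 26 and r = 0.5 the figures are 70%, 18% and 6.3 points. Partial loss is often missed across the whole range. Complete loss is missed often only at the low correlation.

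**Step 2: T1 against T3, no app effect, both arms gaining equally**

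The same formula with n = 22 gives the chance that the experimental-arm paired test is significant:

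- shared gain of 4.6 points: 26% (r = 0.5), 40% (r = 0.7), 67% (r = 0.85);
- shared gain of 9.2 points: 75%, 93%, 99.8%.

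In a simulation with 22 per arm and 4,000 runs per setting (r = 0.5 and 0.85), an ANCOVA of the T3 score on arm and T1 score rejected in 4.4% to 5.4% of runs, whatever gain the arms shared.

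**Step 3: what a T3 comparison would deliver**

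Power of the T3 ANCOVA for a 9.2-point difference: f = 0.59/2 = 0.295 and λ = f²N/(1 − r²). For N = 45 and r = 0.5, λ = 0.0870 × 45/0.75 = 5.22, and power on 1 and 42 df is 0.61.

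| N | r = 0.5 | r = 0.7 | r = 0.85 |
|---|---|---|---|
| 45 | 0.61 | 0.77 | 0.96 |
| 52 | 0.67 | 0.83 | 0.98 |

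The change in the arm difference from T2 to T3 has half-width t × SD of change × √(2/n). At r = 0.5 this is 2.02 × 15.6 × √(2/22) = 9.5 points with 22 per arm, and 2.01 × 15.6 × √(2/26) = 8.7 points with 26 per arm.

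**The case against.** **No rule equates p>.05 with retention.** A reader might infer that the plan will declare retention from a non-significant test. The documents do not support that: no rule, margin or visit pair is written, and a full protocol or analysis plan may hold them. What stands is narrower. The paired test is the only stated evidence on retention, and it is confined to one arm. No choice of visit pair or margin turns it into a controlled comparison.

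**The ANCOVA might cover T3.** A reader might also infer that the control arm's T3 data are discarded. That goes too far. The retention sentence does not name T3, and the abstract applies ANCOVA to primary and secondary outcomes without limiting it to one visit. Still, the labels below Table 1 make T2 the likelier reading. The supportable statement is that no T3 between-group contrast is specified.

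**Retention is peripheral.** It is neither the primary nor the secondary objective, the Anticipated Findings section calls the trial exploratory, and the Limitations concede that "this study focuses on a short-term follow-up period and may not capture the long-term efficacy of the app". This is fair and lowers the severity. It does not make a within-arm test answer a question about the app.

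**The illustration depends on the correlation.** This also stands. The 25% miss rate for complete loss and the 6.9-point half-width hold only at 0.5; at 0.85 they are 0.2% and 3.8 points.

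**The remedy is no more precise.** Correct: at r = 0.5 the change in the arm difference is less precise than the paired change (9.5 against 6.9 points with 22 per arm). The case for the change rests on attribution.

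**The WAST is not validated**, as its own section says, and is absent from the stated objectives. Its omission from the retention sentence is a minor addition.

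**Conclusion.** The point holds as a should-fix. Followed as written, the retention analysis is uncontrolled, and its result cannot be credited to the app under either choice of visits. That conclusion comes from the design and needs no numerical assumption.

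The size of the problem does need assumptions: the back-calculated SD of 15.6, correlations of 0.5 to 0.85, about 22 people per arm, and a hypothetical shared gain for the T1–T3 reading. On these, a T2–T3 test misses loss of half the assumed gain in 33% to 74% of trials. A T1–T3 test credits a shared 4.6-point gain to the app in 26% to 67%. The figures concern the ABC scale only; the protocol gives no SD for the mobility or knowledge measures.

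The documents do not support rating this as a flaw in the primary result. The ANCOVA of postintervention scores on T1 is unaffected.

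**What to change.** Replace the retention sentence with a comparison of arms at T3:

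- Analyse each T3 score by ANCOVA on arm and the respective T1 score. Alternatively, fit one mixed model to T1, T2 and T3 in both arms with arm-by-visit terms, which also keeps people who miss a visit and is available in SPSS.
- Report the T3 between-arm difference with its 95% CI. The change in that difference from T2 to T3 can be added, with its CI.
- Include the WAST, which is already collected at T3.
- Keep within-arm change in the experimental group descriptive, and name the visits compared.
- Base any claim of a sustained app effect on the T3 between-arm estimate, not on a non-significant within-arm change.

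**Cost.** Only the analysis wording changes; no visit, measure or participant is added. Recruitment is expected to run to the end of December 2026. Since 26 people had already completed T3 by November 2025, the change should be recorded before outcomes are examined by arm. The price is precision: power at T3 for 9.2 points is only about 0.61 to 0.67 at a correlation of 0.5, so the report should present the T3 difference as an estimate with its interval.

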### Sample Size

The sample size calculation was based on the Activities-specific Balance Confidence (ABC) scale questionnaire (primary outcome) [43]. No study has reported the minimum clinically important difference for the ABC scale among walking aid users. However, considering a study on 376 patients with knee osteoarthritis who had undergone surgery (many of whom used a walking aid), ABC scores increased by an average of 9.2% 1 year after total knee arthroplasty (repeated measures model; Cohen *d*=0.59) [44]. On the basis of the variability reported in the study [44], an estimated correlation of 0.5 between measurements, including ABC scale and 2 potential covariates (type of walking aid and duration of walking aid use), a sample size of 45 would be sufficient to explore a 2-way difference between groups (*F* tests) in a 2-way repeated measures model (2 groups×2 time points; 1–β=.9; α=.05; G*Power [Heinrich Heine University Düsseldorf]) [45]. With a conservative dropout rate estimated at 15% [46], a total sample size of 52 participants is enough to find significant differences between groups for the primary outcome. To minimize participant dropout and ensure high retention rates, several strategies will be implemented. These include clear and transparent informed consent procedures, regular and supportive communication with participants, and flexible scheduling for study visits. Efforts will be taken to maintain a strong and supportive relationship between the research team and participants. All participants will be reassured about the confidentiality of their data and the importance of their contribution to the success of this study.

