The findings of this study may help improve accessibility to health care by reducing the waiting time between the walking aid prescription, purchase, and training with a health care professional. In fact, while some walking aids are owned independently, others are prescribed by health care professionals, with physical therapists being the most common prescribers [72]. Thus, this app would contribute to reducing the waiting time for walking aid prescriptions and training with a health care professional. For instance, more than 10,000 Canadians were reported to be waiting for occupational therapist or physiotherapist services across Ontario [73], and the median waiting time was more than 6 months for 41% of outpatient publicly funded physiotherapy services in Québec [74]. Improving access to mHealth technologies may help address the growing human health care resource challenges in the world [75] and may also enable access to education for people living in remote or rural areas.

Finally, the results obtained from this pragmatic RCT, especially from sensitivity analysis, may help identify specific factors contributing to improved balance confidence, mobility, and knowledge of walking aid users after using an educational tool, such as the type of walking aid, the previous experience using walking aid, and individual factors such as age and diagnosis. This will enable larger-scale studies to be set up by the type of walking aid or the type of condition necessitating the use of a walking aid.

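### The planned sensitivity analyses are in purpose exploratory subgroup analyses; their factor list does not match the Discussion, and about 45 participants give little power to detect effect modification

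*Protocol article*

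**What the plan says.** Four places in the protocol article bear on this.

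- **Statistical Analysis.** The primary model is an ANCOVA with the T1 score as the covariate. Then: "Sensitivity analyses will also be conducted based on walking aid type, walking aid use experience, previous training, and the main reason for use". No model is given for these analyses. The section also states: "The significance level will be set at .05, and all statistical tests will be 2-tailed".
- **Anticipated Findings.** The trial's results, "especially from sensitivity analysis, may help identify specific factors contributing to improved balance confidence, mobility, and knowledge of walking aid users". The factors then named are aid type, previous experience, age and diagnosis. The results are meant to inform larger studies set up by aid type or by condition. The same section calls the trial exploratory.
- **Limitations.** There will be no stratification by aid type, digital literacy, cognitive level, user experience or education, and responses to the app may vary as a result. "However, sensitivity analyses will help to partially address this issue".
- **Sample Size.** The trial is sized for the overall comparison only ("2 groups×2 time points; 1–β=.9; α=.05"): 45 evaluable, 52 enrolled. The calculation allows for "2 potential covariates (type of walking aid and duration of walking aid use"). The ANCOVA described under Statistical Analysis names only the T1 score.

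**The concern.** A sensitivity analysis re-estimates the same effect under a different assumption, analysis set, model or handling of missing data. Repeating or splitting the comparison by baseline characteristics does something else: it asks whether the effect differs between kinds of participant. The Discussion confirms that this is the aim. Covariate adjustment, which the words *based on* could also mean, would not show who benefits.

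The label matters because a reader of the results may take these analyses as support for the primary finding, or take a pattern across subgroups as a real driver of benefit. The Discussion would carry such a pattern into the design of later trials. The Limitations also offer these analyses as a partial answer to a problem that, for three of its five characteristics, the listed factors do not touch.

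**Working it through.** **1. Factor lists side by side**

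| Characteristic | Statistical Analysis | Anticipated Findings | Limitations (not stratified) |
|---|---|---|---|
| Aid type | yes | yes | yes |
| Use experience | yes | yes | yes |
| Previous training | yes | no | no |
| Main reason for use / diagnosis | yes | yes (as diagnosis or condition) | no |
| Age | no | yes | no |
| Digital literacy | no | no | yes |
| Cognitive level | no | no | yes |
| Education | no | no | yes |

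Only aid type and experience appear in all three. The last three rows are outside the listed analyses at any sample size.

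**2. Inputs for power**

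- Effect: "ABC scores increased by an average of 9.2% 1 year after total knee arthroplasty (repeated measures model; Cohen *d*=0.59"). This is a within-patient change in the cited study; I use 0.59 SD as the assumed group difference. Implied SD: 9.2/0.59 = 15.6 ABC points.
- Correlation: "an estimated correlation of 0.5 between measurements", so the residual SD after adjusting for T1 is √(1 − 0.5²) = 0.866.
- Two-sided α of .05; N = 45 evaluable or 52 enrolled.
- Assumed, because no subgroup sizes are given: two-level factors split 50/50, with other splits shown as a range.

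**3. The plan's own figure.** No power is stated for these analyses. The 45 for the overall comparison does not reproduce from 0.59 and 0.5: with f = 0.59/2 = 0.295, a 2×2 repeated-measures model needs 33 for the group-by-time test and 93 for the between-group test. That is a separate matter. To keep it from driving the result, I compute power from the stated inputs and again granting the stated 90%.

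**4. Overall ANCOVA at N = 45.** SE = 0.866 × 2/√45 = 0.258; noncentrality 0.59/0.258 = 2.28; power about 61%.

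**5. Arm-by-factor interaction.** SE = 0.866 × √(4/(Np) + 4/(N(1 − p))), where p is the share in one level.

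- N = 45, p = 0.5: SE = 0.866 × √(16/45) = 0.516; noncentrality 0.59/0.516 = 1.14; 40 df; power about 20%.
- N = 45, p = 1/3: 18%; p = 1/4: 16%.
- N = 52, p = 0.5: 23%.
- Correlation 0.7 instead of 0.5, p = 0.5: 27% (N = 45) and 31% (N = 52).
- Smallest interaction detectable with 80% power, N = 45, p = 0.5: (2.021 + 0.851) × 0.516 = 1.48 SD, or 1.48 × 15.6 ≈ 23 ABC points.
- Half-width of its 95% confidence interval: 2.021 × 0.516 = 1.04 SD, about 16 ABC points.
- N for 80% power at 0.59 SD, p = 0.5: about 273.

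**6. Granting 90% overall power.** The overall noncentrality is then 1.960 + 1.282 = 3.242. An interaction of the same size with an even split has twice the SE: 3.242/2 = 1.621, and Φ(1.621 − 1.960) = 0.37.

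**7. Within one subgroup, should anyone test there.** Under the assumption of equal thirds by aid type (7 or 8 per arm), power for 0.59 SD is 21–24%.

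**8. False positives, if tests are independent.** The chance of at least one is 1 − 0.95^k.

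- 4 factors on ABC alone, k = 4: 19%.
- 4 factors × 5 outcomes (knowledge and confidence summed into one score), k = 20: 64%.
- 4 factors × 6 outcomes, k = 24: 71%.

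**The case against.** The text is hedged. It calls the trial exploratory, says the analyses may help, and claims only a partial remedy. A reader might infer that the protocol claims it will establish who benefits, or that these analyses make up for the absence of stratification. It claims neither. For aid type and experience the Limitations sentence is fair, since both are in the list and varying response is what subgroup analyses examine.

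A reader might also infer that separate tests at .05 within each subgroup are planned. The article does not say so. It gives no model, and interaction terms or descriptive estimates fit its wording equally well. That detail commonly sits in an analysis plan, so its absence here is no fault.

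Three further points stand. Diagnosis plausibly means the same as main reason for use, so only age is clearly outside the list. The 71% is the top of a range, because the article does not say that every outcome will be analysed by every factor. The subgroup splits are assumptions.

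None of this removes the label, the mismatch between sections, or the low power, which persists under every variant tried.

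**Conclusion.** The point holds in a limited form. The analyses are mislabelled: by their stated purpose they are exploratory effect-modifier analyses. Age is discussed but not listed. The partial-remedy statement can apply only to aid type and experience. Power for an interaction as large as the whole assumed effect is about 20% at N = 45 and 23% at N = 52. It is 16–31% over the splits and correlations tried, and about 37% if the 90% overall power is granted. The chance of at least one false positive is 19–71%, depending on how many outcomes are analysed and assuming independence.

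These figures rest on 0.59 SD as the group difference and on assumed subgroup splits. They do not show that the primary comparison is biased, and they do not show that within-subgroup significance testing is planned. They show that the trial can generate hypotheses about effect modifiers but can hardly confirm or exclude any.

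**What to change.** - Rename the analyses as exploratory subgroup analyses.
- Estimate each arm-by-factor interaction in the full-sample ANCOVA, mainly for ABC. Report the estimate with its 95% confidence interval and make no significance claims within subgroups. Since these tests have only about 20% power, the interval is the useful output.
- Align the factors in Statistical Analysis and Anticipated Findings, either by adding age (already collected at baseline) to the first or dropping it from the second. State the aim as hypothesis generation.
- Limit the Limitations sentence to aid type and experience.
- Add aid type and duration of use, already named as potential covariates under Sample Size, to the primary ANCOVA alongside the T1 score.

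The cost is some rewording, a few interaction models, a few degrees of freedom in the primary model, and fewer headline subgroup results. Recruitment is expected to run to December 2026, so the change can be made before the analysis.
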